## Abstract

**Introduction:** High levels of physical, cognitive, and psychosocial impairments are anticipated for those recovering from the COVID-19. In the UK, ~50% of survivors will require additional rehabilitation. Despite this, there is currently no evidence-based guideline available in England and Wales that addresses the identification, timing and nature of effective interventions to manage the morbidity associated following COVID-19. It is now timely to accelerate the development and evaluation of a rehabilitation service to support patients and healthcare services. Nuffield Health have responded by configuring a scalable rehabilitation pathway addressing the immediate requirements for those recovering from COVID-19 in the community.

**Methods and Analysis:** This long-term evaluation will examine the effectiveness of a 12-week community rehabilitation programme for COVID-19 patients who have been discharged following in-patient treatment. Consisting of two distinct 6-week phases; Phase 1 is an entirely remote service, delivered via digital applications. Phase 2 sees the same patients transition into a gym-based setting for supervised group-based rehabilitation. Trained rehabilitation specialists will coach patients across areas such as goal setting, exercise prescription, symptom management and emotional well-being. Outcomes will be collected at 0, 6, and 12 weeks and at 6- and 12-months. Primary outcome measures will assess changes in health-related quality of life (HR-QOL) and COVID-19 symptoms using EuroQol Five Dimension Five Level Version (EQ-5D-5L) and Dyspnea-12, respectively. Secondary outcome measures of the Duke Activity Status Questionnaire (DASI), 30 s sit to stand test, General Anxiety Disorder-7 (GAD-7), Patient Health Questionnaire-9 (PHQ-9), Patient Experience Questionnaire (PEQ) and Quality Adjusted Life Years (QALY) will allow for the evaluation of outcomes, mediators and moderators of outcome, and cost-effectiveness of treatment.

**Discussion:** This evaluation will investigate the immediate and long-term impact, as well as the cost effectiveness of a blended rehabilitation programme for COVID-19 survivors. This evaluation will provide a founding contribution to the literature, evaluating one of the first programmes of this type in the UK. The evaluation has international relevance, with the potential to show how a new model of service provision can support health services in the wake of COVID-19.

**Trial Registration:** Current Trials ISRCTN ISRCTN14707226

Web: http://www.isrctn.com/ISRCTN14707226

## Introduction

### Clinical Impact of COVID-19

In late 2019 a highly pathogenic novel coronavirus (CoV), severe acute respiratory syndrome (SARS)-CoV-2, emerged, causing a global pandemic with millions of cases worldwide (1). SARS-CoV-2 commonly attacks the respiratory system, leading to hospitalisation with many requiring breathing support advancing in some cases to intensive care support (2). Further complications include those meeting diagnostic criteria for acute respiratory distress syndrome (ARDS), anaemia, cardiac injury and secondary infection (2). COVID-19 is a highly infectious respiratory disease and as a result the COVID-19 pandemic has profoundly impacted the UK population resulting in strict measures to curtail the spread of infection. This disease was unknown in humans and most research has concentrated on the acute phase to reduce mortality. Acute treatment is largely symptomatic and supportive depending on the severity of infection. As of June 2020, there was no specific treatment or vaccination available. Indications show that COVID-19 will have a profound long-term impact on those infected as was previously seen following the MERS and SARS pandemics. MERS survivors showed significantly negatively impacted HR-QoL for up to 14 months post-virus (3) indicating that rehabilitation should be measured in months/years rather than weeks (4).

Data from previous pandemics such as those described, indicates a number of adverse side effects in recovering patients. Long-term ventilatory dysfunction and associated lung damage are common characteristic as are muscle weakness and fatigue (5, 6). Whilst less common, metabolic disorders, including hyperinsulinemia, insulin resistance, hyperglycemia, and type 1 or 2 diabetes were reported in recovering SARS patients (4).

Non-physical morbidity such as psychological morbidity and cognitive dysfunction are also common after a period of critical illness such as COVID-19. It has been reported that 1 in 10 critically ill patients develop severe psychological problems including anxiety, depression and post-traumatic stress disorder (PTSD) (7). Whilst there are a multitude on contributory mechanisms, the potential areas of comorbidity here all represent important target areas within rehabilitation.

It is anticipated that COVID-19 will hospitalise ~150,000 people by the end of 2020. Of those individuals, it is suggested that 50% will require additional rehabilitation support in the community to support improvement in HR-QoL (8) and to reduce burden on NHS services.

### Impact on Rehabilitation Services

The COVID-19 pandemic has acted as a sharp reminder as to the exceptional work of the National Health Service (NHS). As we move further through the pandemic patients are being medically discharged in growing numbers. As patients move out of the acute phase of care it is clear to see the impending burden facing rehabilitation services, described by the Chartered Society of Physiotherapy as an “tsunami of rehabilitation need” (8). Normal health and social care delivery in many countries, including the UK has been deferred in order to support the acute phase of COVID-19. Healthcare interventions aimed at improving or maintaining function such as falls prevention programmes, as well as well-established rehabilitation pathways such as cardiac and pulmonary rehabilitation, are unable to continue, with potential deleterious effects on function. These issues risk worsening health, physical and psychological function for vast numbers of people who may not have suffered from COVID-19 directly (9). As movement restrictions are lifted, the consequences of these indirect effects of the pandemic will become apparent. Prior to the COVID-19 pandemic, to meet the 18-week standard for newly referred patients and clear the backlog of patients who will have already waited longer than 18 weeks, the NHS would have needed to treat an additional 500,000 patients a year for the next 4 years. The pandemic is likely to make waiting lists grow further and the challenge will be even greater (10).

Alarmingly and as has been made clear by National Institute for Health and Care Excellence (NICE) there is currently no evidence-based guideline available in England and Wales that addresses the identification, timing and nature of effective interventions to manage the physical and non-physical morbidity associated following COVID-19 (11). Progress is being made, with an initial framework devised for assessing early rehabilitation needs of COVID-19 patients, following intensive care treatment. Much more work is required to address the spectrum of needs, particularly for those that have not spent time in intensive care (12). Pulmonary rehabilitation has been shown to be successful in improving exercise tolerance and HR-QoL, and has been shown to reduce hospital admissions rates in patients with COPD (13, 14), yet despite the associated severe muscle wastage and deconditioning, on-going dyspnoea, sleep disorders and severe fatigue, memory problems, anxiety, depression, and post-traumatic stress disorder (15), rehabilitation is neither defined or guaranteed for those recovering from COVID-19.

### New Models of Rehabilitation

A rapid expansion in rehabilitation services is necessary to support an increasing number of patients suffering from long-term complications of COVID-19. Given the level of urgency, a more diverse rehabilitation workforce is required to meet the scale of this challenge, using capacity and skills from sectors outside healthcare organisations. Specifically, improved capacity could be achieved by developing rehabilitation capabilities across the wider non-registered health care staff, including specialist trained exercise professionals, to help meet both demand and effective dose and progression of exercise (16).

The Australian healthcare system may provide a strong basis upon which to base a new model of rehabilitation support, utilising the expertise of exercise professionals. Inclusion of exercise professionals within the Australian healthcare sector has resulted in substantial healthcare cost savings with annual well-being gains of $7,967 and $11,847 per person with diabetes and cardiovascular disease, respectively, with a benefit-cost ratio of 9:1 and 6:1 (17).

Compelling data also exist for the cost effectiveness of exercise in the treatment of mental health, dementia and other common chronic diseases (17) The utilisation of exercise professionals to support clinical rehabilitation is something that has been long employed by Nuffield Health, rendering the Charity well-placed to mobilise and investigate the approach with a cohort of COVID-19 survivors. It should be made clear, that at present there is no formal accreditation pathway for clinical exercise physiologists.

Not only is the organisation of personnel key to new models of rehabilitation, but also the mode of delivery. Delivery modality of rehabilitation will be one of the most significant changes as we progress through the Post-COVID-19 phase. To reduce the number of “face to face” consultations and indeed resource strain, remote consultations including telephone and video platforms have evolved significantly to provide a continuity of care (18). Whilst previous uptake of digital rehabilitation options has been poor (19) this delivery approach has been shown to confer positive health and well-being outcomes in participants that showed strong adherence (19–21). As an example, “Activate Your Heart” is a well-established digital cardiac rehabilitation programme and was evaluated in several different locations. Data demonstrated that users' exercise capacity and HR-QoL improved after completing the programme (22).

The restrictive conditions associated with the COVID-19 lockdown and indeed social anxieties as restrictions are lifted, suggest that there will likely be a greater acceptance of digital healthcare from both a patient and clinician perspective (23, 24). Nuffield health has experience in delivering remote digital interventions for mental health, primary care and physiotherapy. The learnings from these areas will be built into the development of the remote COVID-19 rehabilitation programme. The digital component will be evaluated for both clinical effectiveness as well as acceptability from both the clinician and patient perspective.

### Aims

The aim of the present evaluation is to implement and appraise a novel model of community rehabilitation for individuals recovering from COVID-19. The focus will be on the clinical effectiveness of the programme for improvements in HR-QoL and suppression of COVID-19 related symptoms. The specific research questions include the following:

Is HR-QoL improved and are symptoms related to COVID-19 reduced at 6 and 12 weeks post-intervention and are benefits retained at 6 and 12 months?Is a novel blended model (digital and physical) of care cost-effective in the rehabilitation of those recovering from COVID-19?Is a novel blended rehabilitation programme acceptable to both patients and rehabilitation specialists?

We hypothesise that: (a) the 12-week rehabilitation programme will be effective in improving HR-QoL and reducing symptoms related to COVID-19 at 6 and 12 weeks and those benefits will be retained at 6 and 12 months; (b) the blended model will be cost effective when compared to previously described rehabilitation methodologies, specifically outpatient multidisciplinary pulmonary rehabilitation; (c) we expect the programme to be acceptable to both patients and specialists.

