18 years of age and over	Have a formal diagnosis of post-traumatic stress syndrome, clinically significant anxiety or depression where low intensity mental health intervention will not assist
Access to transport for phase 2 attendance	Have been diagnosed with Chronic Fatigue Syndrome

Once referred, the patient will complete an online pre-assessment health questionnaire. Once completed the questionnaire is made available digitally to a specialist trained physiotherapist who will contact the patient to conduct a telephone triage assessment. Following successful triage, the patient is handed on to a rehabilitation specialist who then takes up responsibility of the patients care. All patients will receive the identical 12-week programme structure consisting of two 6-week phases, depicted in Figure 1 and described in detail below.

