### Rehabilitation Programme

NHS healthcare professionals will utilise inclusion/exclusion criteria at the point of discharge to refer a patient to the programme. Alongside the provision of a patient information document, the patient will be fully informed verbally about the programme, being given the opportunity to join the programme should they so wish. The patient will be made aware that their data will be utilised anonymously for research purposes. The patient may also request that their data is not utilised and will still be able to participate in the programme. Should they choose not to progress they will be sign-posted to alternative community/NHS services where available. If the patient accepts to progress on to the programme the NHS healthcare professional will complete an online referral, sent directly to Nuffield Health using a secure online form. Data sharing agreements have been completed between NHS and Nuffield Health and all processes conform to GDPR and NHS digital requirements.When an online referral is completed, an automated booking process is triggered. Via email or telephone (based on patient preference) the patient will choose an appointment time for an initial triage screening. The patient will also be asked to complete pre-screening questions, designed to support the triage process.The patient next joins a telephone or online video triage consultation utilising this feature. The triage is conducted by specialist physiotherapists trained in remote consultation. The triage is designed to be an additional safety step ensuring that the patient is clinically fit to progress onto the 12-week programme. The 45-min triage will also act to collect additional relevant patient information that may be pertinent when tailoring their exercise programme. Information such as details on additional co-morbidities, emotional well-being and medication will be discussed. Should any contraindications to exercise be identified during the triage the patient will be informed that they are unable to progress on the programme at that time. The patient will be sign-posted back to their General Practitioner, who will also be notified in writing. The original referring clinician will also be notified. At the end of triage, if deemed appropriate, the specialist physiotherapist will refer the patient to the rehabilitation specialist with recommendations for the intensity of entry level exercise and specific needs and goals.Following successful triage, the patient will be automatically sent a welcome pack via post as well as email. This will provide full guidance on how to download, access and register on the digital platforms and will provide links to learning materials. The patients GP will also be made aware that their patient has initiated the programme. The digital application platform utilises the functionality of a platform already used extensively across Nuffield Health (MyTherapy, Nuffield Health, London, UK). All other virtual audio-visual communication will be delivered by a separate digital system (Microsoft Teams, Microsoft, Redmond, USA).Within 72 h of referral, the patient will be contacted by their assigned rehabilitation specialist based at a Nuffield Health site within a 20-mile proximity to the referring hospital. practitioner will provide a welcome to the programme, offer the opportunity to ask any questions and to inform them of the start date of the programme.The patient begins the 12-week programme. This programme phases are as follows:

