## Measures

Outcome data will be collected at 0, 6, and 12 weeks and again at 6- and 12-months post-intervention. Self-report data will be collected via digital application (MyWellbeing, Nuffield Health, London, UK). The patient will be emailed and provided a push-notification prompting them to complete the aforementioned questionnaires. Whilst this evaluation will not utilise any formal comparison group, it is intended that collaboration with trusts will support the analysis of anonymised “usual care” outcome data. This is likely to come from community physiotherapy and/or modified pulmonary rehabilitation.

All data will be securely stored on a dedicated Nuffield Health server and will be retained in line with the organisations publicly available data retention schedule. Modifications to data written to the database will be documented through via an internal inquiry system. Data entered into the database will be retrievable for viewing throughout by those granted secure access privileges associated with an identification code and password. Any data errors will be summarised along with detailed descriptions for each specific problem in a data query reports, which will be sent to the study Outcomes Analyst. The Outcomes Analyst will check any inconsistency, checking other sources to determine required corrections. Any coding changes required within the digital data capture system will then be implemented within 24 h.

Complete back up of the primary database will be performed twice a month. Incremental data back-ups will be performed on a daily basis. In addition to system back-ups, additional measures will be taken to back-up and export the database on a regular basis at site level. The outcomes analyst will send weekly email reports with information on missing data, missing forms, and missing visits to site level co-ordinators who will then rectify immediately as and when required. Data security audits will be completed by the Nuffield Health Information Security group on a quarterly basis. Full details of group membership and details of audit processes can be provided upon request.

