### Costs

EQ-5D-5 L utilities will be reported alongside the full evaluation costs of the intervention so as to elicit a “per head” economic evaluation of all participants recruited (35).

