Examining potential mediators and moderators of change will contribute to our understanding of key processes in achieving improvement in services using blended models of rehabilitation. Whilst mediators and moderators of rehabilitation outcomes have been explored, this will be the first exploration of a combined digital/physical intervention. This will inform the tailoring of interventions to best address the needs of the targeted population, ultimately leading to the development of more effective interventions.

An area requiring on-going review and indeed development relates to the provision and impact of rehabilitation across sociodemographic groups. Black, low-income, and immigrant communities are particularly vulnerable and disproportionately impacted by COVID-19 (36, 37). Furthermore, data exists indicating that secondary care-based clinics may be underused by older populations and those in poorer socioeconomic circumstances (37). The proposed evaluation will ensure that sociodemographic variation is considered within analysis and that a representative sample from those that are disproportionately affected are consulted post-programme to understand barriers and facilitators. It is critical that learnings are continuous and that they are built into future re-iterations of the rehabilitation programme.

The proposed economic analysis will add to the current literature in regard to evidence of the cost-effectiveness of home or web-based rehabilitation programmes and will be an innovative analysis of a clinical rehabilitation programme ran independently of allied health professionals within a non-NHS community environment. In a context of health care provision where resources are now especially stretched, cost-effective interventions can only support the delivery of effective health services.

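### Hypothesis (b) claims cost-effectiveness against outpatient pulmonary rehabilitation, but the economic analysis described has no comparator and cannot test it

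*Protocol article*

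**What the plan says.** Research question 2 in the Aims section asks whether the blended model is cost-effective for people recovering from COVID-19. Hypothesis (b) supplies the comparator: "the blended model will be cost effective when compared to previously described rehabilitation methodologies, specifically outpatient multidisciplinary pulmonary rehabilitation".

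The economic method is one sentence in the Costs section: "EQ-5D-5 L utilities will be reported alongside the full evaluation costs of the intervention so as to elicit a" per-head "economic evaluation of all participants recruited". Both the costs and the people belong to the programme.

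The design is a single treated cohort. Under Trial Design, "All patients will receive the identical 12-week programme structure". The Measures section adds: "Whilst this evaluation will not utilise any formal comparison group, it is intended that collaboration with trusts will support the analysis of anonymised" usual-care outcome data, and says these would probably come from community physiotherapy, modified pulmonary rehabilitation, or both. The Statistical Analysis section plans mixed effects models of change over time and describes no between-service or cost comparison.

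The Abstract nevertheless promises an evaluation of cost-effectiveness, and the Discussion presents the economic analysis as adding to the cost-effectiveness evidence on home and web-based rehabilitation.

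**The concern.** Cost-effectiveness relative to another service is an incremental quantity: the difference in cost set against the difference in QALYs, over the same horizon. Hypothesis (b) is of that kind and names the alternative. The Costs section produces a description of one service. The two do not meet.

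If the plan is followed as written, the final report will hold a mean cost per participant and a set of utilities, and will have to answer a comparative question with them. A reader would probably take the utility change from baseline as the programme's benefit. These patients are recovering from a hospital admission for acute illness, so some improvement is to be expected without any programme, and a single cohort cannot separate the two.

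What is at stake is the answer to one of three research questions and one of three hypotheses. The primary outcomes are not affected by the mismatch.

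**Working it through.** The article gives no cost, QALY, threshold or sample-size figure for hypothesis (b), so there is no stated number to reproduce. The check is which of the required quantities the plan supplies.

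**Quantities needed.** Write C for mean cost and Q for mean QALYs per patient, with PR for outpatient multidisciplinary pulmonary rehabilitation:

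- incremental cost = C(programme) − C(PR)
- incremental QALYs = Q(programme) − Q(PR)

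**Quantities supplied.**

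| Term | Where in the article | Status |
|---|---|---|
| C(programme) | Costs | planned |
| Q(programme) | Primary Outcome Measures (EQ-5D-5L as QALY source); Costs | planned |
| C(PR) | nowhere | not planned |
| Q(PR) | Measures, intended usual-care outcome data | not secured |

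The Q(PR) entry falls short in three ways. Obtaining the data is an intention, not a commitment. The data are called outcome data, and the article does not say that EQ-5D is among them. The likely sources are community physiotherapy and modified pulmonary rehabilitation, which are not the outpatient multidisciplinary service named in hypothesis (b).

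Two of four terms are available, both for the programme. Neither difference can be formed from the analysis described.

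**What the single cohort does give.** Let e be the programme's effect on utility and r the recovery that would have occurred without it. The observed change from baseline is e + r. With no comparator, only the sum is observed, so e is not identified. The article describes referral at discharge (Rehabilitation Programme) and also after a 12-week post-discharge follow-up (Patient and Public Involvement). On either description patients enter while recovering, so r cannot be assumed to be zero.

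**How r bears on hypothesis (b).** With a concurrent comparator in similar patients, the difference would be (e + r) − (e(PR) + r) = e − e(PR), and recovery would cancel. With published pulmonary rehabilitation figures from a stable chronic disease, r would enter on the programme's side only. The pulmonary rehabilitation benefit cited in the Introduction is in COPD. The article does not say which kind of comparator would be used, so neither the size nor the direction of any error against pulmonary rehabilitation can be worked out from it.

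**The case against.** The strongest defence has three parts.

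First, hypothesis (b) refers to methods already described, which may mean an informal benchmark against published pulmonary rehabilitation figures; the Costs section cites a reference for its approach, and a condensed article may leave economic detail to a fuller plan. This stands in part. It is why the conclusion is limited to the analysis described and does not say that the hypothesis is untestable in principle. It does not remove the conflict: the article states a comparative hypothesis, a non-comparative analysis and the absence of a formal comparison group, and names no comparator cost, source or threshold. Omitted unit costs or discount rates would be condensation; this is not.

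Second, the intended usual-care data from the trusts could serve as the comparator. They could help with outcomes, but no costs are mentioned, and the services differ from the one in the hypothesis.

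Third, the Aims section puts the focus on clinical effectiveness, and the Abstract lists QALYs among the secondary outcomes. That is right, and it limits the severity.

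Two stronger readings are tempting, and the documents support neither.

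- A reader might infer that physiotherapist time will be left out of the costing, because the Discussion calls the programme one "ran independently of allied health professionals within a non-NHS community environment" whereas under Rehabilitation Programme "The triage is conducted by specialist physiotherapists trained in remote consultation". But the Costs section refers to the full costs of the intervention and excludes nothing, and the Discussion sentence is not a costing rule. It may describe only who runs the sessions after triage. The wording needs reconciling; no omitted cost is shown.
- A reader might infer that the cost per QALY will be understated by a calculable factor. That would apply to a ratio against no treatment, which the plan never specifies, and would rest on an assumed share of natural recovery. It says nothing about the comparison with pulmonary rehabilitation.

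**Conclusion.** The point holds as a mismatch between a stated comparative claim and a stated non-comparative analysis. Hypothesis (b), and research question 2 as that hypothesis frames it, cannot be tested by the analysis described: two of the four quantities needed are planned, comparator cost is absent, and comparator QALYs are not secured. Any utility change from baseline will include natural recovery of unknown size.

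No numerical size can be put on the consequence, because the article gives no cost, utility or comparator figure. The extent is one research question and one hypothesis out of three each, with the primary outcomes untouched. The conclusion assumes that the Costs section is a fair account of the economic method; a fuller plan that specifies a pulmonary rehabilitation comparator would supply the missing analysis, but the article's statements would still need to be brought into line with it. Severity: should be fixed.

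**What to change.** **Preferred: match the claim to the analysis.** Restate research question 2 and hypothesis (b) as a cost-consequence description: mean cost per participant, and mean EQ-5D-5L utility at 0, 6 and 12 weeks and at 6 and 12 months, each with a confidence interval. Remove the comparative claim of cost-effectiveness from the Aims, Abstract and Discussion, and state that change from baseline includes natural recovery. This costs wording only and needs no new data.

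**If the comparative claim is kept.** Name the source of pulmonary rehabilitation costs and QALYs, whether published figures or trust data. Specify the incremental cost and incremental QALY analysis over a common horizon, with its uncertainty. Say how differences between the patient groups will be handled. State plainly that this needs comparator costs and utilities beyond the outcome data mentioned in the Measures section. This option is not free: those data would have to be requested from the trusts or drawn from a named publication.

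**In either case,** reconcile the Discussion's description of a programme independent of allied health professionals with the physiotherapist triage set out under Trial Design and Rehabilitation Programme. This too is a wording change.
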